## Abstract

**Background:**

Stress levels in the general population had already been increasing in recent years, and have subsequently been exacerbated by the global pandemic. One approach for innovative online-based interventions are “chatbots” – computer programs that can simulate a text-based interaction with human users *via* a conversational interface. Research on the efficacy of chatbot-based interventions in the context of mental health is sparse. The present study is designed to investigate the effects of a three-week chatbot-based intervention with the chatbot ELME, aiming to reduce stress and to improve various health-related parameters in a stressed sample.

**Methods:**

In this multicenter, two-armed randomised controlled trial with a parallel design, a three-week chatbot-based intervention group including two daily interactive intervention sessions *via* smartphone (á 10–20 min.) is compared to a treatment-as-usual control group. A total of 130 adult participants with a medium to high stress levels will be recruited in Germany. Assessments will take place pre-intervention, post-intervention (after three weeks), and follow-up (after six weeks). The primary outcome is perceived stress. Secondary outcomes include self-reported interoceptive accuracy, mindfulness, anxiety, depression, personality, emotion regulation, psychological well-being, stress mindset, intervention credibility and expectancies, affinity for technology, and attitudes towards artificial intelligence. During the intervention, participants undergo ecological momentary assessments. Furthermore, satisfaction with the intervention, the usability of the chatbot, potential negative effects of the intervention, adherence, potential dropout reasons, and open feedback questions regarding the chatbot are assessed post-intervention.

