### Intervention

2.6.

ELME is a rule-based, conversational chatbot and was developed by members of the Department of Clinical and Health Psychology and the Institute of Distributed Systems at Ulm University. This type of technology is a self-developed, web-based chatbot platform, provided *via* smartphone with SMS notifications. The input modality is written; the output modality is also written, except audio files provided by the chatbot.

The chatbot-based intervention aims at stress reduction and improving health-related parameters such as interoception and mindfulness. In particular, the intervention contents mainly address the constructs of stress, interoception and mindfulness as well as their association, provided *via* psychoeducation and exercises (e.g., audio files such as breathing exercises) in a real-time dialogue with the chatbot. The intervention units are offered twice a day with one session in the morning and one session in the afternoon or evening over the course of three weeks, depending on the self-selected time of a participant. The times of the units could be switched daily *via* a settings menu in the chatbot platform. In the weekends, only one session takes place, the day can be freely selected by each participant. Importantly, the contents and exercises aim to be closely related to everyday life. Therefore, the chatbot asks questions related to current situations of the participants and exercises are designed short (10–20 min). The gender-neutral persona of the chatbot is characterized by a friendly demeanor as an empathetic companion with expertise in mental health. ELME's communication style can be described as calm, tolerant, supportive, and appreciative. For each start of a session with ELME, the participant receives an SMS. Furthermore, participants receive reminder SMS to fulfill the units with ELME and they could postpone single exercises to one hour later. Participants have to complete each session within three hours; otherwise ELME aborts the session automatically to assure the course of upcoming sessions. Moreover, the chatbot platform menu provides answers to frequently asked questions, a download function for the audio files and summaries of the single exercises.

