##### Negative effects

2.8.2.15.

The Inventory for the Assessment of Negative Effects of Psychotherapy (INEP; 123) assesses potential negative effects of psychotherapy (e.g., intrapersonal change, relationships, or stigmatization). The scale comprises 21 items, including four items which are rated on a 7-point bipolar scale (−3 = “worse; + 3 = “better”), calculated to mean scores with lower values reflecting more negative effects. The other items are rated on a 4-point Likert scale ranging from 0 = “not at all” to 3 = “totally agree”. In the present study, an 18-item version adapted to possible negative effects of the chatbot-based intervention (e.g., excluding items regarding the therapist) is used to assess potential negative effects of the chatbot-based intervention. The original questionnaire exhibited a high internal consistency with a Cronbach's Alpha of 0.86 (123).

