##### Adherence

2.8.2.16.

According to the suggested guidelines regarding adherence in randomised controlled trials investigating online interventions (124), adherence to the intervention is operationalized by the percentage of completed intervention units. All assessed variables, the according measurement instruments and measurement points are depicted in Table 2. Reasons for potential dropout reasons are assessed *via* the Dropout Reasons Questionnaire for Internet Interventions (125).

**Table 2 T2:** Assessed variables, measurement instruments and measurement points.

Variables	Measurement instrument	Measurement point				
		T0	T1	T1–T2	T2	T3
Primary outcome						
Acute perceived stress	Perceived Stress Scale (PSS-10)	X				
Acute perceived stress	Perceived Stress Scale - short form (PSS-4); 2 items (EMA)		X	X	X	X
Secondary outcomes						
Demographic variables (e.g., age, gender, pre-experience with chatbots)	Demographic Questionnaire		X			
Self-reported interoceptive accuracy	Interoceptive Accuracy Scale		X		X	X
Self-reported interoceptive accuracy	Awareness Scale of the Body Perception Questionnaire		X		X	X
Self-reported interoceptive accuracy	Interoceptive item (EMA)			X		
Body Awareness	Body awareness items (EMA)			X		
Mood	Visual Analogue Mood Scale (EMA)			X		
Mindfulness	Freiburg Mindfulness Inventory – short form (FMI)		X		X	X
General anxiety	General Anxiety Disorder (GAD-7)		X		X	X
Depression	Patient Health Questionnaire (PHQ-8)		X		X	X
Personality	Big Five Inventory (BFI-10)		X			
Emotion regulation	Emotion Regulation Questionnaire (ERQ)		X		X	X
Psychological well-being	WHO-5 Well-Being Index		X		X	X
Stress mindset	Stress Mindset Measure (SMM)		X		X	X
Intervention credibility and expectancies	Credibility / Expectancy Questionnaire (CEQ)		X			
Affinity for Technology	Affinity for Technology Interaction (ATI)		X			
Attitudes towards Artificial Intelligence	Attitudes towards Artificial Intelligence (ATAI) Scale		X		X	X
Satisfaction with the intervention	Client Satisfaction Questionnaire (CSQ-8)				X	
Usability of the app	Mental Health App Usability Questionnaire (MAUQ)				X	
Negative effects of the intervention	Inventory for the assessment of Negative Effects of Psychotherapy (INEP)				X	X
Adherence	Percentage of completed intervention units				X	
Dropout reasons	Dropout Questionnaire				X	
Open feedback questions regarding the chatbot					X	

Notes. EMA, ecological momentary assessment.

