### Sample size estimation

2.9.

The sample size was calculated by an a-priori power analysis for a repeated measurement ANOVA *via* G*Power (126), comparing two groups. Assuming a small effect size of *f* = 0.15 (consistent with *d* = 0.30), based on an *α*-level of 0.05, a power of 0.90, and a dropout rate of 40%, the sample size analysis resulted in *N* = 130 participants (*n* = 65 in the intervention group, *n* = 65 in the control group). As previous findings regarding chatbot-based interventions in the area of mental health are sparse, the assumed effect size of *d* = 0.3 was determined based on a systematic review (127), reporting effect sizes of *d* = 0.29 for depression and *d *= 0.15 for anxiety. A review and meta-analysis based on online mindfulness-based interventions stated small effect sizes for mindfulness (*g* = 0.32), depression (*g* = 0.29), anxiety (*g* = 0.22), and well-being (*g* = 0.23). It needs to be noted that results regarding adherence, respectively, attrition rates in online or chatbot-based interventions are also sparse or often not reported (124, 55). The dropout rate of 40% is estimated based on the systematic review of adherence to web-based interventions (128) and the adherence rates of guided interventions (39, 45, 46).

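### Negative effects and dropout reasons are scheduled only from t2 onward, with no stated collection when a participant stops, so people lost before t2 would be absent from these data

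*Protocol article*

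**What the plan says.** The timing is given in two places, and they agree.

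- **Abstract, Methods:** "potential negative effects of the intervention, adherence, potential dropout reasons, and open feedback questions regarding the chatbot are assessed post-intervention".
- **Section 2.8.2.16 and Table 2:** Table 2 is presented as showing every variable, instrument and measurement point. It lists the "Inventory for the assessment of Negative Effects of Psychotherapy (INEP") at T2 and T3, and the dropout questionnaire at T2 only. The text names the latter as the "Dropout Reasons Questionnaire for Internet Interventions".

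Section 2.8.2.15 says that an 18-item adapted version of the INEP "is used to assess potential negative effects of the chatbot-based intervention". It is the only dedicated negative-effects instrument in Table 2.

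Section 2.9 plans 130 participants, 65 per arm, with 40% dropout. That figure "is estimated based on the systematic review of adherence to web-based interventions" and on adherence rates of guided interventions.

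Between t1 and t2 the article describes two sources of data: daily momentary ratings of stress, body awareness, interoception and mood (section 2.8.2.2), and the record of completed units (section 2.8.2.16). The platform can tell when a session goes unfinished. Participants have three hours, "otherwise ELME aborts the session automatically to assure the course of upcoming sessions" (section 2.6). Phone numbers and e-mail addresses are verified at registration (section 2.4), and reminders go out by SMS (section 2.6).

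**The concern.** Both instruments matter most for people who stop early, yet both are tied to a calendar date at or after the end of the three-week intervention. Someone who stops in week 1 is first asked why about two weeks later. If that person has also left the study by then, neither question is answered at t2.

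The protocol names dropout reasons as a means of improving the intervention (section 2.1 is preceded by this aim at the end of the Background) and names poor long-term engagement as a limitation (Discussion). If the answers come mainly from people who stayed, a finding of few negative effects could partly reflect who was still there to answer, and the dropout reasons would describe only those who stopped the chatbot but kept answering questionnaires.

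**Working it through.** **1. What the sample size implies about missing people.** Inputs from section 2.9: N = 130, 65 per arm, 40% dropout.

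- Expected dropouts: 0.40 × 130 = 52; with equal dropout by arm, 0.40 × 65 = 26 in the chatbot arm.
- Remaining: 130 × 0.60 = 78, or 39 per arm.

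The plan's 130 can be reproduced as 78/(1 − 0.40) = 130. Here 78 is the size needed for a repeated-measures ANOVA group-by-time interaction with f = 0.15, α = 0.05 and power 0.90, for m = 3 measurements and an assumed correlation ρ = 0.6 between them. The noncentrality is f²·N·m/(1 − ρ) = 0.0225 × 78 × 3/0.4 = 13.16, with 2 and 152 degrees of freedom. The article gives neither m nor ρ. With ρ = 0.5 and m = 3 the result is 96, or 160 after inflation. The present point does not depend on ρ. It uses only the fact that dividing by 0.60 treats the 40% as giving no usable outcome data.

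**2. Who is missing under the schedule.**

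| Participant | Dropout reason (T2 only) | INEP (T2, T3) |
|---|---|---|
| Stops the chatbot, still answers t2 | yes, in retrospect | yes |
| Lost before t2, returns at t3 | no | t3 only |
| Lost before t2, never returns | no | no |
| Lost between t2 and t3 | already asked at t2 | t2 only |

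The gap is rows 2 and 3 for dropout reasons and row 3 for the INEP. The ceiling of 26 applies if all dropout falls in row 3.

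**3. Effect on the observed negative-effect rate.** Let r be the true rate in the chatbot arm, d the overall proportion lost, and q the proportion lost among those affected. Then

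observed rate = r(1 − q)/(1 − d).

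The documents give neither r nor q. Assume r = 10% (6.5 of 65) and take d = 40%, the ceiling:

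| q | Affected and still answering | Observed among 39 |
|---|---|---|
| 20% | 5.2 | 13.3% |
| 40% | 3.9 | 10.0% |
| 60% | 2.6 | 6.7% |
| 80% | 1.3 | 3.3% |
| 100% | 0 | 0% |

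At q = d there is no bias; below it the bias is upward. The 80% row leaves 26 − 5.2 = 20.8 dropouts among the 58.5 unaffected participants (35.6%), so it needs affected people to leave a little more than twice as often as the rest.

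If only half the allowance is lost before t2 (assumed d = 20%, so 52 answer) and affected people are lost at twice that rate (q = 40%), the observed rate is 3.9/52 = 7.5%.

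**4. Precision.** If no negative effect is seen, the exact one-sided 95% upper bound is 1 − 0.05^(1/n): 7.4% for n = 39 and 4.5% for n = 65. This loss occurs whatever q is.

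**5. Whether other data fill the gap.** The momentary items record mood and stress, but do not ask about negative effects or why someone stopped. They run on the chatbot platform (section 2.4), so they may well end when a participant disengages. The unit record shows that someone stopped, not why. Imputation (section 2.10) has little to work with: the INEP has no t1 value, so a person in row 3 has no INEP observation, and a standard model would fill in values from those who stayed.

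**The case against.** A reader might infer that the whole 40% will be missing from the harm data. The documents do not support that. The figure comes from adherence literature, so it may partly describe people who stop using an intervention rather than leave a study. The t0–t3 questionnaires run on a separate survey tool (section 2.4), the analysis is by intention to treat, and nothing says that people who stop the chatbot are not sent t2 and t3. A dropout questionnaire at t2 makes sense for exactly those people. Neither the timing of dropout nor its split by arm is given. This objection stands: 26 is a ceiling, not an expectation.

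A reader might also infer that the negative-effect rate is certain to be too low. That requires affected people to leave more often than others. This is plausible, but the documents give no figure for it, and at equal dropout there is no bias.

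Daily mood and stress ratings, including negative emotions, give an indirect signal up to a participant's last response, and anxiety and depression are measured at t1, t2 and t3. This stands in part: the momentary ratings could show worsening before departure, but do not attribute it to the chatbot. The anxiety and depression scales are next due at t2 and share the same gap.

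Finally, the article is condensed, and a fuller protocol might describe contact at discontinuation. It cannot be said that the platform makes no such contact. But the timing is not a detail left out: the article states it, in a table offered as complete and in the abstract. As written, it contains no assessment at stopping.

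**Conclusion.** The point holds as a limitation of the stated schedule. Participants lost to assessment before t2 would be absent from the dropout-reason data and, unless they return at t3, from the negative-effects data.

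The size is up to about 26 of 65 in the chatbot arm, assuming equal dropout by arm, all of it before t2, and no later response. Any downward bias is conditional on affected people leaving more often than others; the illustrated fall from 10% to 6.7% or 3.3% rests on assumed rates of 60% and 80% and on that ceiling.

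The primary outcome is unaffected. This is a cheap improvement to the secondary harm and dropout-reason data, not a flaw that threatens the trial's main conclusion.

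**What to change.** In Table 2 and sections 2.8.2.15–2.8.2.16, add an event-triggered assessment:

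- On withdrawal, or after a run of aborted or unstarted sessions whose length is fixed in advance, the platform automatically sends a link to the Dropout Questionnaire and the adapted INEP.
- Keep t2 and t3 for everyone, and say explicitly that this includes people who stopped using the chatbot.
- Report negative effects for all who started the intervention. Show answers given at discontinuation, at t2 and at t3 separately, because length of exposure differs, and state how many never answered.

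The cost is one automated message rule. The contact details, the SMS system and both questionnaires already exist, and treatment, randomisation and the primary outcome do not change. The downsides are a few extra prompts to people who have stopped, incomplete response among them, and INEP answers given after differing lengths of exposure. The change narrows the gap but does not close it.

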**Discussion:**

To the best of our knowledge, this is the first chatbot-based intervention addressing interoception, as well as in the context with the target variables stress and mindfulness. The design of the present study and the usability of the chatbot were successfully tested in a previous feasibility study. To counteract a low adherence of the chatbot-based intervention, a high guidance by the chatbot, short sessions, individual and flexible time points of the intervention units and the ecological momentary assessments, reminder messages, and the opportunity to postpone single units were implemented.

**Trial registration:**

The trial is registered at the WHO International Clinical Trials Registry Platform *via* the German Clinical Trials Register (DRKS00027560; date of registration: 06 January 2022). This is protocol version No. 1. In case of important protocol modifications, trial registration will be updated.

## Background

1.

Stress levels in the general population had already been increasing in recent years, and have subsequently been exacerbated by the global pandemic. In particular, 64% of a representative German adult sample feel stressed at times and 26% feel stressed frequently (1). 77% of the latter stated that they experience life today as more stressful than 15–20 years ago. As the two central reasons for the high stress experience, school, studies, or work as well as high demands on themselves were reported. These are followed by the illness of a closely related person as a source of stress which might be associated with the COVID-19 pandemic (1). Systematic reviews and meta-analyses based on studies investigating stress, anxiety, and depression prevalence among the general population during the COVID-19 pandemic worldwide (2, 3), showed a mean prevalence of stress between 30% and 37%, 24 to 31% for the prevalence of anxiety, and 28% to 34% for the prevalence of depression. Consistently, the numbers of mental disorders increase, resulting in the main reason for days absent due to illness (4). Moreover, the International Classification of Diseases, 11th Revision (ICD-11), was extended by a category of stress-related mental disorders (5), which underlines the relevance of stress and the need for interventions of stress reduction.

One approach to cope with stress and different related psychological disorders is mindfulness-based interventions. Mindfulness has been conceptualized as a state of being aware and focused on the present moment in an open, accepting and non-judgmental way (6–9). Previous meta-analyses and reviews showed positive effects of online mindfulness-based interventions on mental health outcomes such as decreases in perceived stress (e.g., 10–12), anxiety (e.g., 11, 12), depression (e.g., 11, 12) as well as increases in mindfulness (e.g., 10, 11) and well-being (e.g., 11).

Another health-related, closely related construct to stress is interoception. Interoception is defined as the process of the nervous system of sensing, interpreting, and integrating internal bodily signals (13) such as cardiovascular, respiratory, or gastrointestinal signals to a moment-by-moment internal bodily landscape across conscious and unconscious levels (14, 15). According to a recent classification model of interoception by 16 (16), a distinction between accuracy and attention to interoceptive signals (i.e., factor 1) and between objective measures and self-reported beliefs concerning interoceptive signals (i.e., factor 2) is made. Previous research indicated associations between interoceptive abilities and stress (e.g., 17–21). In particular, a study by Schultchen and colleagues (20) found that a decreased objective interoceptive accuracy is associated with higher long-term stress. Moreover, several studies showed that interoceptive abilities are associated with emotional abilities (e.g., 22, 23) and that they are impaired in diverse mental disorders such as anorexia nervosa (e.g., 24), depression (e.g., 25), or schizophrenia (26). An increasing body of research indicates that interoceptive abilities can be trained, for example, *via* mindfulness-based interventions (e.g., 27, 28), body-focused training such as power posing (29), or heartbeat perception training (30, 31). So far, online interventions to improve interoceptive abilities are sparse. An ongoing study (32) investigates the effects of a guided online mindfulness-based intervention on stress, interoceptive abilities and further health-related parameters. Integrating such trainings into everyday life might be a promising approach (31).

In the past few years, there has been a growing interest in the use of and the research about chatbots (33–35). A “chatbot” or conversational agent is defined as a computer program, which is able to simulate a text-based interaction with human users *via* a conversational interface (e. g., *via* website or smartphone; 36, 33). Chatbots can be classified into different categories such as application domain (i.e., domain-specific knowledge support), service provided (i.e., scripted dialogs vs. query interface for information retrieval), or according to the response generation method (i.e., rule-based selection of pre-defined text components vs. natural language processing and machine learning-based responses; 33, 37). Other characteristics of chatbots comprise the type of interaction interface, i.e., the device on which the chatbot interacts with the user (e.g., mobile application, web browser), or the input and output modality (written, spoken, or mixed), among others (38).

Chatbot-based interventions provide advantages such as low-threshold and anonymous use, flexibility regarding time and location of use, and cost-effectiveness; therefore, they could be integrated easily into everyday life (39–43). Moreover, especially the effects due to guided online interventions (i.e., intervention contents are accompanied or provided by a guide such as an e-coach or even a chatbot) to improve mental health need to be highlighted (44, 11), as they showed higher adherence rates (39, 45, 46) and were more effective in terms of symptom severity reduction (47) as compared to unguided interventions. Social motivation might be an essential factor in the effectiveness of chatbot-based interventions (34, 48). Mental health apps including psychoeducation, also *via* a chatbot, have shown to provide the potential to decrease stigma, e.g., *via* the use of the chatbot and educational strategies (49), and to increase mental health literacy (39, 42, 50, 51). Particularly, lacking awareness of available support was revealed as a substantial barrier to mental health access in young people (52, 53). Additionally, previous research on chatbots supports their potential to deliver psychoeducation and to promote self-adherence (54).

In the application of chatbots to improve mental health, research on the efficacy of chatbot-based interventions is still sparse (37, 38, 55). A mixed-method systematic review based on chatbot-based interventions for mental health (56) showed significant decreases in psychological distress with effects ranging from small (*d* = 0.24) to very large (*d* = 2.0). In particular, the improved outcomes comprised depression (57–59), psychological distress (60), anxiety (58), fear of heights (61), and positive affect (58, 60). Moreover, these findings are also summarized in the reviews by (54) and (55), inter alia, including the findings of increased well-being (60). In contrast, for example, a pilot study by (62) found neither significant improvements in perceived stress nor in psychological well-being in a non-clinical sample due to a two-week smartphone-based intervention. This intervention was based on positive psychology and cognitive-behavioural therapy provided by a chatbot in comparison to a wait list control group. Nevertheless, this sample included only 28 participants, and, results revealed significant effects when only including the adherent participants (i.e., in this study, those participants with at least 25% activity and not being inactive for more than 7 days or more in a row). Similarly, the findings by (63) showed significant reductions in self-reported symptoms of depression in high users compared to the low user group. In contrast, for a two-day chatbot-based therapeutic writing intervention aiming to improve psychological well-being, good feasibility, but no effects on well-being were demonstrated (64, 65). Both improved well-being and stress reduction due to a three-week chatbot-based stress management intervention were reported in a sample of young adults (66). Comparably, a recent study (67) found significantly reduced stress levels and decreased anxiety in students due to a 4-week chatbot-based intervention based on cognitive behavioral therapy, mindfulness techniques, and positive psychology. It needs to be considered that both studies (66, 67) were uncontrolled. To sum up, previous studies differ in various aspects such as the study design, the intervention duration, outcome assessments, primary goals of the chatbot, type of communication technology, input and output modality, and their samples. There is still a lack of standard measures and randomized controlled trials of chatbot-based interventions in the mental health area (55, 68, 38, 35). Moreover, standards for chatbot-based mental health apps are missing (39, 42). Consequently, more structured randomized controlled trials on chatbot-based interventions to improve specific parameters of mental health such as stress or anxiety based on standard measures and guideline-based chatbots are needed.

We developed a three-week chatbot-based intervention *via* smartphone comprising two daily short sessions (á 10–20 min.) for a sample with medium to high stress levels, aiming to improve stress and health-related parameters such as interoception and mindfulness. The chatbot is named ELME, a gender-neutral name as an acronym for Everyday-life Mindfulness Experience. The intervention duration was determined based on previous studies investigating chatbot-based interventions ranging from two to four weeks (e.g., 67, 69, 62; 60, 66) and reported preferences of an adult sample for short online sessions (70). Considering the target group of the intervention, namely, a stressed sample, short sessions were found to be effective to reduce perceived stress and individuals seem to use intervention exercises more frequently if they take less time (71).

According to the CONSORT Consolidated Standards of Reporting Trials (CONSORT) 2010 Guidelines for randomized controlled trials (72, 73) and the according extension for randomised pilot and feasibility trials (74), we conducted several pilot phases and a feasibility study (DRKS00025446) based on a sample size of *n* = 44 with usability as assessed *via* the mHealth App Usability Questionnaire (75) as the primary outcome variable and the design of the actual study. Results showed that the chatbot-based intervention is a feasible and flexible tool. User feedback was implemented to an optimised version of the chatbot used in the current study. Aiming to increase adherence, this adapted version of ELME includes even shortened units, the setting to switch the training time slots for the next day and an adaptation of the favoured typing speed of ELME. The present study investigates the effects on diverse health-related and user-oriented parameters.

We hypothesize that:
(1)the primary outcome perceived stress will be reduced in the intervention group compared to the treatment as usual control group.(2)the secondary outcomes interoception, mindfulness, and psychological well-being will be improved.Furthermore, we examine potential changes in secondary outcomes as health-related and related to the primary and main secondary outcomes, but not directly in the intervention targeted variables, e.g., depression, anxiety, emotion regulation, stress mindset and test for potential modifying effects on an exploratory level. For example, stress mindset could be a moderating factor of perceived stress (76, 77). Moreover, similar health-related measures had been investigated in the reported previous online or chatbot-based intervention studies (e.g., 55, 65–67). Additionally, based on previous research, we investigate user-oriented parameters such as usability, satisfaction with the intervention, and, lastly, adherence and potential dropout reasons, to potentially further improve the intervention for future research.

